### Sample

2.2

Sample size was calculated using G*Power 3.1.9.7 software (41), considering a repeated measures ANOVA design with two groups (experimental *vs.* control) factors, and two measurement times (pre *vs.* post). The estimated minimum sample size at alpha 0.05 and statistical power of 80%, for moderate effect size (f = 0.25), was approximately 34 subjects (17 per group). At baseline, participants will be pre-screened using an online questionnaire to determine eligibility.

The inclusion criteria were: (i) minimum age of 18; (ii) at least one year of competitive football experience; (iii) no eye problems that impair vision; (iv) no history of neurological injuries; (v) abstinence of caffeine, alcohol and intense physical activities in the previous 24 h before each experimental session; (vi) having slept for at least 7 h the night before. On the other hand, the exclusion criteria were: history of neurological injury; uncorrected vision problems; diagnosis of psychological disorders; use of psychoactive substances in the last 24 h before the experimental sessions; any form of nystagmus for electrophysiological contraindications for electrophysiological recording. The operationalization and description criteria are summarized in Table 1.

**Table 1 T1:** Sample operationalization and description criteria.

Topic	Description	Operationalization
Age	Minimum age of 18 years	Participants aged 18 years or older. There is no maximum age limit stipulated in the protocol.
Gender	Gender balance	Sample of 24 men and 24 women, in equal number for experimental and control groups.
Competitive experience	Minimum of 1 year of competitive experience	Football players with a minimum of 1 year of regular practice in competitive condition
Health condition	No conditions preventing the practice of sport	Individuals with a history of neurological injuries, uncorrected visual problems, diagnosed psychological disorders, use of psychoactive substances in the last 24 h, or any clinical limitation to physical exertion will be excluded. Pregnant women will also be excluded.
Legal and ethical criteria	Compliance with current regulations	The study complies with the GDPR and the provisions of Decree-Law No. 5/2007, ensuring that all participants meet the legal and ethical conditions for physical exercise.

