#### Technical and motor performance

2.5.3

Technical and motor performance will be assessed using the LSPT and the Y-SART, using Witty SEM indicators (Microgate, Bolzano, Italy). These instruments allow the effects of mental fatigue on technical execution, reactive agility and decision-making processes in a sporting context to be quantified with high temporal precision and reliability.

Comparisons between groups will examine whether the ST induces greater impairments in performance metrics compared to a cognitively neutral task. The LSPT will provide data on total execution time, technical penalties, and adjusted score, while the Y-SART will produce reaction and execution times in response to visual stimuli. These comparisons will elucidate the degree to which mental fatigue affects motor fluency, visuomotor coordination, and accuracy under pressure.

Intra-subject analyses in the experimental group will allow for the detection of performance deterioration caused by the ST. By comparing pre- and post-intervention scores on both the LSPT and Y-SART, this approach will help determine whether mental fatigue results in statistically significant reductions in motor and technical efficiency.

The associations between performance metrics and indicators of fatigue (e.g., VAS, EEG, and ETS) will also be examined to explore whether higher levels of perceived or physiological fatigue correlate with slower and less accurate performance. These relationships may help identify which dimensions of fatigue are most predictive of declines in physical performance.

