##### VAS

2.5.4.2

The VAS for mental fatigue, applied immediately before and after the cognitive induction task (ST), captures acute fluctuations in the subjective perception of fatigue. This 100 mm continuous scale, anchored between “no fatigue” and “extreme fatigue”, is sensitive to short-term changes induced by cognitive load and task duration (84). Within the experimental group, VAS ratings will be compared pre and post ST to quantify the immediate impact of the intervention on mental fatigue.

In addition, associations between subjective fatigue and other objective markers will be explored. Specifically, post-intervention VAS results will be correlated with EEG spectral characteristics (particularly alpha and theta power), oculomotor parameters (blink rate, pupil diameter, saccadic dynamics, and fixations), and motor performance measures (LSPT and Y-SART). This approach allows us to determine whether higher levels of self-reported fatigue align with neurophysiological and behavioral indicators of reduced performance, providing a multimodal framework for validating the perceptual dimension of fatigue.

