For EEG data (theta, alpha, and beta bands), spectral power within predefined regions of interest (ROIs) will be analyzed using repeated-measures models including Time (pre vs. post mental fatigue) and Recording Condition (eyes open, eyes closed, motor imagery), allowing evaluation of fatigue-related changes across neural states. Primary analyses will focus on frontal midline and posterior ROIs, consistent with the study's theoretical hypotheses. Exploratory analyses across additional scalp regions will be conducted separately and corrected using False Discovery Rate (FDR) procedures to control for multiple comparisons. Correlational analyses (Pearson's r) will explore associations between EEG bands and behavioral performance (LSPT, Y-SART), as well as subjective fatigue scores (VAS and FAS) (94, 95). Topographic maps will be generated to visualize EEG power distributions across cortical regions.

For oculomotor parameters (fixations, saccades, pupil diameter, blink rate), comparisons will assess the impact of mental fatigue on attention dynamics and visual search efficiency. Pearson correlations will explore links between ETS metrics, EEG patterns, and motor performance scores. Eye-tracking outcomes will be interpreted in conjunction with EEG measures, motor performance variables, and subjective fatigue scores, allowing a multimodal framework that reduces interpretative ambiguity.

Motor performance will be analyzed by comparing LSPT and Y-SART results before and after cognitive induction. Metrics such as execution time, technical penalties, and reaction times will be examined to determine whether cognitive fatigue impairs decision-making and technical execution under pressure.

These performance results will be correlated with neurophysiological and oculomotor indicators to investigate predictive relationships. Subjective fatigue will be analyzed using pre and post VAS comparisons and baseline FAS scores. These will be used to triangulate subjective perceptions with objective changes in EEG, ETS, and performance data. Higher self-reported fatigue scores are expected to align with reduced cortical efficiency, altered visual behavior, and degraded motor output.

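### The post-intervention VAS is correlated with other markers without an arm or baseline term; if the arms are pooled, the group difference biases the correlations read as convergence

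*Protocol article*

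**What the plan says.** Section 2.5.4.2 (VAS) collects the VAS before and after the cognitive task but selects the later level for the association analysis: "post-intervention VAS results will be correlated with EEG spectral characteristics (particularly alpha and theta power), oculomotor parameters", and also the LSPT and Y-SART. The stated aim is to see whether self-report lines up with the objective markers and so to validate the perceptual side of fatigue.

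Section 2.6 (Statistical analysis) gives the method as Pearson's r. These analyses "will explore associations between EEG bands and behavioral performance (LSPT, Y-SART") and with VAS and FAS scores; a further sentence applies Pearson correlations to eye tracking, EEG and motor scores. Section 2.5.3 plans to "explore whether higher levels of perceived or physiological fatigue correlate with slower and less accurate performance". Sections 2.5.1.2 and 2.5.6 use the results to judge convergence between modalities and the validity of fatigue assessment.

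No correlation is given a term for arm or for the marker's own baseline. The covariates listed in sections 2.5.5 and 2.6 are demographic and contextual.

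Two things are left open. Only the VAS is fixed as a post-intervention level; the time point of the EEG, eye-tracking and motor values is not stated. Nor does the text say whether the two arms are pooled.

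**The concern.** The hypothesis at the end of the Introduction is that the Stroop task moves every domain: self-report, EEG, gaze and performance. Under that hypothesis, randomised arm is a common cause of both variables in each correlation. A pooled r is then expected to differ from zero even if, within each arm, a player's reported fatigue says nothing about that player's EEG or passing score. Part of the convergence result would restate the group difference.

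A second, separate route runs through stable differences between players, such as skill or habitual alpha power. If such traits are correlated across modalities, post-intervention levels correlate too, whether or not any fatigue was induced.

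What is at stake is the reading of the correlations as evidence that the markers validate one another. This matters because sections 2.5.1 and 2.5.1.2 accept that EEG changes are not specific to fatigue and rely on the other modalities to interpret them.

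**Working it through.** **1. The plan's own figure.** Section 2.2 describes a calculation "considering a repeated measures ANOVA design with two groups (experimental" versus control) and two times, with alpha 0.05, power 80% and f = 0.25, giving "approximately 34 subjects (17 per group"). The correlation between repeated measures is not stated; 0.5 is assumed here. For the Time × Group test, λ = f²·N·m/(1 − ρ) = 0.0625 × 34 × 2/0.5 = 8.5 on 1 and 32 degrees of freedom. Power is 0.807, and 34 is the smallest even N that reaches 80%, so the stated figure reproduces.

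**2. What that effect means in SD units.** In a 2 × 2 interaction, f = 0.25 is a cell effect of ±0.25 SD. The between-group difference in change is therefore 4 × 0.25 = 1.0 within-cell SD. With equal baselines, this is a post-intervention shift of d = 1.0. All other shifts below are assumptions, since the article gives no marker SDs or expected shifts.

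**3. Correlation induced by arm.** Take zero association within each arm, unit within-arm SD, 1:1 allocation, and shifts d1 and d2. The arm indicator has variance 1/4, so the pooled covariance is d1·d2/4 and the pooled variances are 1 + d1²/4 and 1 + d2²/4. Hence

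r = d1·d2 / √[(d1² + 4)(d2² + 4)].

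- d = 0.5 and 0.5: 0.25/4.25 = 0.06
- d = 1 and 0.5: 0.5/√(5 × 4.25) = 0.11
- d = 1 and 1: 1/5 = 0.20
- d = 1.5 and 1: 1.5/√(6.25 × 5) = 0.27
- d = 2 and 1: 2/√(8 × 5) = 0.32

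**4. How often this is significant.** Two-sided 5% test, 40,000 simulated trials per scenario, 17 per arm:

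| VAS shift, marker shift (SD) | Induced r | Pooled r significant | r partialled on arm significant |
|---|---|---|---|
| 0.5, 0.5 | 0.06 | 6.5% | 5.2% |
| 1, 0.5 | 0.11 | 9.4% | 5.1% |
| 1, 1 | 0.20 | 20.9% | 4.9% |
| 1.5, 1 | 0.27 | 35.1% | 5.0% |
| 2, 1 | 0.32 | 47.2% | 5.1% |

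The critical |r| at N = 34 is 0.339. Table 1 gives a different total ("Sample of 24 men and 24 women, in equal number for experimental and control groups"). At 24 per arm the induced r is the same, but the pooled rejection rates rise to 27.7% for shifts of 1 and 1, and 62.9% for 2 and 1.

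**5. Stable differences between players.** Suppose there is no arm effect and no correlated change, a pre-post correlation of 0.5, and a trait correlation c between two markers. Post levels then correlate at 0.5 × c. For assumed c of 0.3, 0.5 and 0.7 this is 0.15, 0.25 and 0.35, significant in about 13%, 30% and 54% of trials at N = 34. Change scores give r = 0 and about 5%.

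**6. Change scores alone are not enough.** At a pre-post correlation of 0.5, the SD of a change is √[2(1 − 0.5)] = 1. The same arm shifts therefore induce the same r in changes as in post levels. The arm term and the baseline adjustment address different problems, and both are needed.

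**The case against.** The strongest objection concerns what is actually fixed. Only the VAS is tied to the post-intervention time point. Sections 2.5.6 and 2.6 elsewhere speak of changes in the other domains, and no sentence says that the arms are combined. Sections 2.5.1.2 and 2.5.2 describe prediction under fatigue, and in several sections the correlation text follows an analysis confined to the experimental group. If the correlations were run within arm, the arm effect in steps 3 and 4 would vanish. This stands as a limit on the point. Pooling is still the more natural reading, because the article labels other analyses as within the experimental group and does not label the correlations so.

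A second objection is that such detail belongs in an analysis plan, and that the regression models in section 2.6 might include group. That would answer a complaint about silence alone. But the article makes positive choices, the post-intervention VAS level and Pearson's r, and attaches a validation claim to them.

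Third, between-arm variation could be regarded as the signal of interest, since arm is the fatigue manipulation. The group comparisons already answer that question. Whether players who report more fatigue also show more of the other markers is an individual-level question.

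A reader might infer that every correlation is fixed on post levels, or that the group difference by itself manufactures convergence. The documents support neither. In every scenario in the table the expected r lies below the critical value of 0.339, and even shifts of 2 and 1 SD leave 52.8% of trials non-significant.

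**Conclusion.** The point holds in a limited form. The VAS is fixed as a post-intervention level, the method is plain Pearson's r, and no arm or baseline term is named for any cross-domain correlation. If both arms are pooled and both markers shift, r is biased away from zero and its error rate is inflated. The effect is negligible for shifts of 0.5 SD on each marker (6.5% significant), about fourfold the nominal rate at the planning effect on both (20.9%), and larger if the VAS responds strongly (47.2% at 2 and 1 SD).

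These figures assume pooling, post-intervention values for both variables, no association within arms, and the stated shifts. The trait figures assume trait correlations of 0.3 to 0.7 and a pre-post correlation of 0.5. The analyses are exploratory and the group comparisons are unaffected. The exposed conclusions are those on convergence and validation in sections 2.5.1.2, 2.5.4.2 and 2.5.6. The change is worth making before data are analysed.

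**What to change.** State in section 2.6, and align section 2.5.4.2 with it, that:

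- cross-domain associations use pre-to-post changes, or post values adjusted for their own baseline;
- group is partialled out, or correlations are estimated within arm and then pooled;
- the FAS, which section 2.3 collects only at the start of the session, enters as a baseline characteristic and not as a marker of induced fatigue;
- any unadjusted pooled r is labelled as including the group difference.

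For eye tracking, confirm that a baseline recording exists. Section 2.5.2 plans a pre-post comparison, but the Phase 5 wording in section 2.4 can be read as introducing the recording only at the repeat tests.

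The cost is analysis wording and one degree of freedom (31 instead of 32 at N = 34). The correlations will probably be smaller than the unadjusted ones. Change scores can be less reliable than levels; baseline-adjusted post values lessen that.

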#### Individual variability

2.5.5

Interindividual variability in responses to mental fatigue will be analysed to identify personal and sporting factors that modulate the impact of cognitive overload on neural, visual, and motor performance. This analysis will help clarify how specific athlete profiles cope with mental fatigue and maintain performance efficiency under cognitive stress.

Demographic and contextual variables such as age, gender, field position, training experience, sleep habits, caffeine consumption, and injury history will be considered. These parameters will be used as exploratory covariates to examine their moderating effect on the changes observed in the EEG, ETS, LSPT, and Y-SART results. Recent literature indicates that such individual factors modulate susceptibility to fatigue and help explain the variability in cognitive and physical performance under mental load (10, 13, 85).

This analysis will enable the differentiation of profiles that are more or less sensitive to mental fatigue, helping to map individual patterns of cognitive and physiological response to prolonged cognitive activity. It is expected that athletes with higher levels of competitive experience and attention self-regulation will show smaller decreases in performance and smaller neurophysiological changes. This personalized approach, integrated with objective and subjective data, will contribute to the development of individualized strategies to optimize cognitive and neuromotor resilience in demanding sporting environments.

While individual characteristics will be considered as exploratory covariates, the present sample size and experimental structure are primarily oriented toward detecting overall fatigue-related effects rather than complex interaction models between multiple individual variables. Future studies specifically designed to recruit more homogeneous samples (e.g., athletes from the same competitive level or age group) may allow a more in-depth analysis of interindividual variability in mental fatigue responses.

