During the previous phase, participants will receive specific instructions by e-mail one week before the experimental session, specifying preparation procedures to ensure standardized test conditions.

Upon arrival at the controlled laboratory setting (Phase 1), participants will first be reminded of the study procedures and objectives. After confirming their understanding, each participant will sign an informed consent form, in accordance with the General Data Protection Regulation (GDPR) and Portuguese legislation (Decree-Law No. 5/2007), ensuring ethical compliance and fitness for sports-related assessments. Adherence to pre-test instructions will then be verified, followed by the administration of a structured questionnaire to collect sociodemographic and sports-related information (age, gender, position on the field, training experience, weekly training load, sleep habits, caffeine intake, and history of injury). This data will be used to contextualize participants and control potential confounding variables. These variables may be considered as exploratory covariates in secondary statistical analyses to examine potential moderating effects of competitive experience and contextual factors on fatigue-related outcomes. However, the study is primarily powered to detect main fatigue-related effects rather than complex interaction models.

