**Figure 3 F3:**
[figure not shown]
Schematic representation of the Y-SART, adapted from Yuan et al. (2).

After completing Phase 3, participants move on to Phase 4, where they perform the cognitive intervention defined by their group assignment, either the ST (experimental group) or a neutral task, such as reading magazines (control group). This is followed by Phase 5, which begins with participants completing the VAS again. Next, both motor tests are repeated, this time with continuous recording by the ETS. Finally, a second EEG recording is performed under the same conditions as in the initial phase, concluding the data collection session.

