#### Oculomotor parameters (ETS)

2.5.2

Oculomotor parameters will be monitored using the Pupil Pro Eye Tracking Headset (Pupil Labs GmbH, Germany) to assess neurophysiological changes associated with mental fatigue induced by the ST. The metrics analysed will include the number and average duration of fixations, the duration and average speed of saccades, pupil diameter, and blink rate, parameters widely recognized as sensitive indicators of cognitive load, attention regulation, and fatigue-related decline in vigilance (69–72). To minimize potential confounding influences, standardized task instructions, calibration procedures, controlled lighting conditions, and consistent testing environments will be implemented. Moreover, the within-subject pre-post design allows each participant to serve as their own control, thereby reducing the impact of inter-individual variability in visual strategies and perceptual tendencies.

In addition to descriptive characterisation, the study will include comparisons between the experimental and control groups in terms of these oculomotor parameters after the intervention phase. These comparisons will assess whether mental fatigue induced by the ST produces significant changes in visual-attentional dynamics compared to a cognitively neutral task. Specific attention will be given to variations in blink rate, pupil diameter, fixation duration, and saccade characteristics.

Within the experimental group, oculomotor parameters will be compared before and after the intervention to identify the direct impact of cognitive overload on visual attention and eye movement control. This intragroup analysis is crucial for understanding the dynamic response of the oculomotor system to cognitive stress.

In addition, correlational analyses will be performed between ETS data and behavioral performance on the LSPT and Y-SART to explore whether visual-attentional indicators predict motor performance under fatigue. A multimodal approach will also be employed to assess convergence between different markers of fatigue (ETS, EEG, and VAS), providing a comprehensive understanding of how different modalities reflect fatigue-related changes.

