## Conclusion

4

This protocol proposes an innovative and integrated approach to studying the effects of mental fatigue on the motor performance of football players, combining subjective (VAS, FAS), neurophysiological (EEG), visual (ETS) and performance (LSPT, Y-SART) measures. By articulating these dimensions in the same quasi-experimental design, the aim is to capture more completely and realistically how mental fatigue manifests itself and compromises sports performance.

The main contribution of this study lies in its multimodal and sports-contextualized nature, offering a methodological model that can be replicated in research environments and applied to sports practice. This integration allows us not only to understand the immediate effects of fatigue, but also to advance in the recognition of patterns that may signal states of cognitive vulnerability in athletes.

From a practical point of view, the expected results can inform coaches, physical trainers, and sports psychologists about the importance of monitoring cognitive load in training. Early identification of signs of mental fatigue will allow for adjustments to training volume, the introduction of appropriate recovery strategies, and the personalization of interventions aimed at preserving athletes' decision-making capacity and motor efficiency. In the medium term, this methodology and experimental protocol may also serve as a basis for the development of monitoring technologies and systems that incorporate cognitive indicators into load control, contributing to performance optimization and the prevention of errors and injuries in high-performance contexts.

This protocol offers a rigorous and ecologically-grounded framework for examining how acute mental fatigue shapes neurophysiological activity, visual exploration, and football-specific performance. By integrating EEG, eye tracking, subjective ratings, and validated technical and agility tests within a single experimental structure; this protocol addresses key methodological gaps in the existing literature and provides a template that can be replicated and extended in different football settings.

The findings generated from this approach support more individualized monitoring of cognitive load, and inform training and recovery strategies; thereby helping practitioners better manage mental fatigue to optimize decision-making and technical execution in high-pressure football contexts.

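### Individual patterns, sensitivity profiles and individualized monitoring are claimed from one pre-post change per player, without using the control arm to gauge retest noise

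*Protocol article*

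**What the plan says.** Section 2.5.5 (Individual variability) sets the aim: "Interindividual variability in responses to mental fatigue will be analysed to identify personal and sporting factors". Age, gender, field position, training experience, sleep, caffeine and injury history are to be exploratory covariates that may moderate the observed changes in EEG, eye tracking, LSPT and Y-SART. The result is stated without reservation: "This analysis will enable the differentiation of profiles that are more or less sensitive to mental fatigue, helping to map individual patterns". Section 2.6 (Statistical analysis) names the method as ANCOVA or subgroup analyses.

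Two other places go further. Section 2.5.6 (Multimodal integration) expects composite markers that combine into multidimensional fatigue profiles, and reads preserved performance alongside altered markers as possible compensation. Section 4 (Conclusion) says: "The findings generated from this approach support more individualized monitoring of cognitive load".

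On the design, each player is allocated to either the Stroop task or magazine reading (section 2.2). After that task the performance tests are run a second time: "Next, both motor tests are repeated, this time with continuous recording by the ETS" (section 2.4). No assessment is repeated under the same condition. Section 2.5.2 relies on the pre-post structure: "the within-subject pre-post design allows each participant to serve as their own control".

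The caveats concern power and model complexity. Section 2.2 says "the study is primarily powered to detect main fatigue-related effects rather than complex interaction models", and the end of section 2.5.5 makes a similar statement about sample size and experimental structure.

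**The concern.** A player's observed change is the sum of the average effect, that player's own departure from the average (if any), and retest noise. With one change per player, the last two cannot be told apart. Using each player as their own control removes stable differences between players. It does not remove variation within a player from one test to the next.

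The documents give no figure for that variation. LSPT retest reliability is described only in words (section 2.5.3.1), and section 2.5.1 concedes that the EEG device is less reliable than medical-grade equipment. The control arm follows the same schedule and so offers an internal reference for noise, but no stated analysis compares the spread of change between arms. The caveats do not mention noise either.

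At stake is the applied message. Individual patterns and individualized monitoring could be offered to practitioners when the same spread of changes would occur if every player responded identically. The average comparison between groups is not affected.

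**Working it through.** **1. The plan's own figure.** Section 2.2 gives the design ("considering a repeated measures ANOVA design with two groups (experimental *vs.* control) factors, and two measurement times (pre *vs.* post") and the result: "The estimated minimum sample size at alpha 0.05 and statistical power of 80%, for moderate effect size (f = 0.25), was approximately 34 subjects". For the group-by-time interaction, λ = f²·N·m/(1−ρ), with m = 2 and F on 1 and N−2 df. The correlation ρ is not stated. With ρ = 0.5, λ = 0.0625 × 34 × 2 / 0.5 = 8.5 and power is 0.807; N = 32 gives 0.781. So 34 is reproduced at ρ = 0.5. That is an inferred planning value, not a reliability estimate.

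**2. The powered effect.** In this formula f = 0.25 corresponds to a between-group difference in change of 4f = 1.0 outcome SD.

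**3. Noise in one player's change.** With equal SDs at both times, SD of change = √(2(1−r)) when there is no true heterogeneity. If every player truly declines by δ, the share who appear not to decline is Φ(−δ/SD of change). The expected best-to-worst range among 17 identical responders is about 3.6 times the SD of change (simulated). All figures are in outcome SDs. The correlation r and the effect δ are assumptions, shown over a range.

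| r | SD of change | No decline, δ = 0.5 | No decline, δ = 1.0 | At least 1 of 17 not declining, δ = 1.0 | Expected range |
|---|---|---|---|---|---|
| 0.5 | 1.00 | 31% | 16% | 95% | 3.6 |
| 0.7 | 0.77 | 26% | 10% | 83% | 2.8 |
| 0.8 | 0.63 | 22% | 6% | 63% | 2.3 |
| 0.9 | 0.45 | 13% | 1% | 19% | 1.6 |

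At r = 0.5 the noise SD of one player's change equals the whole powered effect.

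**4. Covariate-defined profiles.** Here retest noise is residual error, and each test keeps its 5% false-positive rate. Over the seven named covariates, the chance of at least one false positive for one outcome is 1 − 0.95⁷ = 0.30 if the tests are independent; simulation gave 0.30.

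**5. What the control arm can show.** The individual-response SD is √(SD_exp² − SD_con²), and the typical error is SD_con/√2. With 17 players, the 95% CI for an SD runs from 0.74 to 1.52 times the estimate. If the response SD equals the retest SD of change, the variance ratio is 2. A two-sided 5% F test on 16 and 16 df (critical value 2.76) then has 26% power. Table 1 of section 2.2 implies 24 per arm rather than 17; that would give 37%. At 17 per arm, 80% power needs a variance ratio of about 4.2, meaning a response SD √(4.2 − 1) ≈ 1.8 times the retest SD of change.

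**6. Should that comparison gate the moderator tests?** Take a binary moderator, split evenly, whose interaction equals the whole powered effect (1.0 SD) at r = 0.5. It adds 0.25 to the experimental-arm variance, so the ratio is 1.25. The variance test would find a larger experimental-arm variance in about 6% of trials, while the direct interaction test has about 29% power. A gate would block most real moderators that a direct test could find.

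**The case against.** The strongest reply is that the plan never classifies players by their own change. Sections 2.5.5 and 2.6 define profiles by measured characteristics, label the covariates exploratory, and count no non-decliners. This stands. A reader might infer that profiles will emerge from noise even if all players respond alike. For the covariate analyses the documents do not support that, because false findings arise there only at chance rates. Nor should the 31% be read as a share the trial will report as resilient. It shows how far a single change score can mislead, and it comes from the least favourable corner of the assumed range. Section 2.5.3.1 claims excellent LSPT reliability, which would point to the lower rows of the table, although no coefficient is given.

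A second reply is that the caveat in section 2.5.5 covers experimental structure as well as sample size and leaves deeper work on interindividual variability to later studies. That tempers the claim, but it does not address retest noise, and the promise in the same section remains unconditional.

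A third is that the paired t-tests planned in each group already require each arm's SD of change, and further reporting may be left to an analysis plan not shown. It is true that the ingredients will exist. The point, however, is an inference the article itself states in sections 2.5.5, 2.5.6 and 4, not a missing reporting detail. The monitoring sentence in section 4 does refer to the whole approach rather than to section 2.5.5 alone, so it needs a condition, not deletion.

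**Conclusion.** The point holds for individual-level readings of change. One pre and one post assessment under one condition cannot separate a player's own response from retest noise, and the stated analyses do not use the control arm to gauge that noise. With an identical true decline of 0.5 to 1.0 SD and a pre-post correlation of 0.5 to 0.9, between 31% and 1% of players would appear not to decline. The range is wide because the documents give no reliability figure.

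The calculation assumes normal changes and equal variances before and after. Using controls as the reference further assumes that retest noise is the same in both arms and that players do not differ in their response to reading.

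It would go too far to conclude that the covariate analyses are invalid, or that the trial can say nothing about variability. It can describe the spread of change by arm, though imprecisely, and it can explore moderators. This is a low-cost improvement to a secondary claim.

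**What to change.** - In sections 2.5.5 and 2.6, report for each outcome the SD of change in each arm, the signed difference in variances (expressed as an individual-response SD) with a 95% CI, and the typical error (control-arm SD of change divided by √2). Keep the sign, because with no heterogeneity the difference is negative about half the time.
- State that precision is low: 26% power at 17 per arm if the response SD equals the retest SD of change.
- Do not make the exploratory moderator tests depend on this comparison.
- In section 2.5.5, replace the promise that the analysis enables differentiation of profiles with a statement that it will explore them. Say that no single player will be labelled resilient or sensitive from one change score, and apply the same limit to the profiles in section 2.5.6.
- In section 4, make the individualized-monitoring statement conditional on evidence of response heterogeneity beyond control-arm variation.

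The cost is a few lines of text and simple calculations on data already to be collected. The price is that the profile and monitoring claims will probably be weaker.
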